## **2.2. Objectives**

This project aims to determine the feasibility of utilizing digital platforms to collect active and passive data related to mental health symptoms among adult outpatients with TRD receiving clinical treatment at the IPP and evaluate the association between the digital data collected with the treatment outcomes of relapse, remission and response. The proposed digital platforms include (1) a wearable device (Oura Ring) to capture passive data on activity, sleep and physiological parameters, and (2) a web-based clinical data management platform (REDCap) to capture responses to validated clinical scales (PHQ-9 and GAD-7) and clinical assessments (MADRS, intake form, demographics) conducted as part of patient care.

The REDCap platform will be available to all participants enrolled in this study; this platform will enable the clinical team to record participants' self-reported symptoms in an electronic platform outside the medical electronic health records system for use in research. Oura Ring use

will be optional and will depend on: 1) device availability, 2) participant's interest, and 3) participant's ownership of a smartphone compatible with the Oura App (to sync and visualize data). We anticipate that approximately 60 Oura Rings will be available for participants to use. Participants will be able to visualize their passively captured data (e.g., activity, sleep parameters, heart rate, respiratory rate, body temperature) on the Oura App in near real-time. These data streams have the power to enable a fine-grained understanding of a patient's experience through means of continuous data collection, visualization, and self-monitoring.

This study has the following aims:

- **Primary Aim:** To examine the feasibility of a digital suite (REDCap clinical scales and a wearable device; Oura Ring) to collect active and passive data, respectively, among adults receiving clinical treatment at the IPP for TRD.
- **Secondary aims:**
  - To evaluate the association of active data (from REDCap) and passive data (from the Oura Ring) over the duration of clinical treatment with the outcomes of treatment response (reduction of  $\geq 50\%$ ), remission (score  $\leq$  clinical threshold), and relapse (score  $\geq$  clinical threshold after initial remission).
  - To create personalized digital phenotype profiles (pDPPs) based on wearable and web-based data.

### ***2.2.1 Personal Digital Phenotype Profile Definition***

We propose the definition of digital phenotype profile (DPP), which calculates an individual's baseline and continuously monitors for changes in DPP characteristics derived from mathematical models. Digital phenotype profile (DPP) is a representation of a user's physical and behavioural health using the baseline data collected at the beginning of the study as reference. The models are then fine-tuned with the continuous incoming data streams. However, variations of the model representations require further investigation to ensure its accuracy and robustness. This work investigates the statistical aspect of the analysis pipeline to offer a robust DPP representation. Specifically, the use of robust principal component analysis (RPCA) to extract sparse representation. The DPP is developed through our Statistical, Information Theory,

and Data-driven (SID) pipeline, then is represented through the sparse-rank matrix using RPCA. Once the DPP representation has been created, we additionally enhance this definition by proposing the term pDPP as a personalized version of the DPP, where we use collected longitudinal data to monitor the changes in physical and behavioural health of an individual participant.

The process of digital phenotyping involves building a mathematical model using the active and passive data collected from each participant. An individual model is built for each person by incorporating their physiological data together with their self-reported affective states collected from questionnaires. Once the personal profile/model has been constructed, physiological data (such as that collected from the Oura Ring) can be used to provide insight into a person's affective state, even without any active data. In the long run, such models could allow for insights into patients' mental well-being in a non-intrusive way that can improve mental health care and responses to stress.

### **3. METHODS**

#### **3.1. Study Design**

This observational study with retrospective data analysis will assess the feasibility of multimodal digital platforms to collect active (self-report) and passive (wearable biometrics) data and enable self-monitoring of adult patients receiving clinical treatment for TRD. Specifically, we will assess the feasibility of using a web-based electronic data capture platform (REDCap) and a wearable device (Oura Ring) to collect active and passive data, respectively, in tandem with neuropsychiatric treatment for TRD in the IPP. The overall duration of this study is three years. However, each participant will only be enrolled in this study for the duration of their clinical treatment in the IPP. All participants will begin participation during the first study visit (known as the Screening and Baseline Visit), which will take place upon scheduling of the first treatment session. For participants receiving the Oura Ring, the Screening and Baseline Visit will occur in-person (so they can obtain an Oura Ring) and will take place approximately three weeks before the first treatment session, to establish baseline parameters measured by the Oura Ring. For participants not receiving the Oura Ring, their clinical treatment can begin after the

Screening and Baseline Visit (usually ~0-3 weeks after), therefore, some participants may complete these measures at their first treatment session .

Following REB approval, 200 patients aged 18 years or older will be recruited over 33 months and will have their self-report assessments (GAD-7 and, if applicable, PHQ-9) entered on the REDCap platform for use in research (see Appendix A). Depending on the availability of Oura Ring devices, a subset of participants will also be offered the opportunity to use an Oura Ring, which is a wearable device that will collect data on sleep, activity, and physiological data in near real-time during their participation in this study. We estimate that approximately 60 Oura Ring devices will be available for participants to use. Potential participants will be adults with TRD enrolled for clinical treatment at the IPP at St. Michael’s Hospital, Unity Health Toronto (SMH-UHT). Participants will receive one of the clinical treatments at the IPP according to clinical protocols and standard of care (Figure 1). The details of the study design are summarized in Figure 2.

[figure not shown]

Figure 2: Study design. Upon enrollment to the IPP, all participants will complete an intake form (including demographics and medical history), will be allocated to one IPP treatment arm based on the intervention decision hierarchy, and informed consent to participate in digital data collection will be obtained. For participants eligible and interested to receive an Oura Ring, they will complete an in-person Screening and Baseline Visit approximately three weeks before the first treatment session to receive their

wearable device and establish a reliable physiological baseline prior to the onset of treatment. Participants not receiving an Oura Ring can begin study participation on the first day of treatment. Duration of treatment will be dependent on the type of intervention participants are receiving, in accordance with standard administration protocols.

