[figure not shown]

Figure 1 - Overview of current clinical research arms for TRD within the Interventional Psychiatry Program. Consenting patients with TRD referred to the IPP will first undergo rTMS. In case of persistent failure to achieve clinical remission, and provided there are no contraindications, patients then undergo IVK treatment and, if necessary, ECT. This study will incorporate a digital mental health suite (mobile assessments and wearable devices) in addition to the treatment-as-usual process in the IPP.

In the Interventional Psychiatry Program (IPP), rTMS is the first treatment arm for patients with TRD. rTMS is a safe, effective, non-invasive neuromodulation therapy for MDD based on the use of magnetic fields to modulate neural circuitry involved in emotion regulation and depressive symptoms. Specifically, it works by directly stimulating specific areas of the brain using focused electromagnetic field pulses that are applied using a magnetic coil placed against the scalp, over the prefrontal cortex. These pulses stimulate specific parts of the brain and are applied repeatedly to strengthen or weaken connections within the brain, leading to long-lasting changes in brain activity. This change is known to reverse unhealthy and abnormal patterns of brain activity that are associated with major depression. With repeated treatments, the magnetic pulses change the activity of the brain cells (neurons) and the pathways between brain cells, returning the brain to normal functioning.

Intravenous ketamine is the second intervention arm in our treatment algorithm. Ketamine is a general anesthetic with analgesic properties approved more than 50 years ago and is on the World Health Organization's list of Essential Medications as an anesthetic. Over the last 20 years, ketamine has been examined in sub-anesthetic doses to treat psychiatric disorders,

including individuals who have not responded well to conventional treatments. Several short-term studies have shown that ketamine is able to reduce depressive symptoms and suicidal thoughts among patients with TRD. A standard ketamine treatment is administered through IV infusions 2 times per week for 3 weeks, and every infusion lasts for about 40 minutes. Additionally, ketamine's antidepressant effects have a rapid onset (within hours) and could be sustained after repeated infusions.

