The last treatment arm in the IPP comprises ECT, which is reserved for patients who fail to respond to rTMS and IVK. ECT is a safe and effective treatment for several mental health conditions, including depression, bipolar disorder, and schizophrenia, which have not improved from other treatments. Also, it may be considered the most effective treatment modality in psychiatry and with robust anti-suicidal effects. ECT involves administering a brief, controlled electrical current between two electrodes applied on the surface of the scalp or temple. The current stimulates a specific part of the brain and causes a small, controlled seizure which lasts between 15 and 90 seconds, and the whole procedure is performed under general anesthesia.

In this study, we will be assessing the uptake and feasibility of using a web-based platform (Research Electronic Data Capture – REDCap) and a wearable device (Oura Ring) to collect data from adults receiving treatment for TRD, using the following metrics: number of recruitments, recruitment rates, dropout rates and reasons for dropping out, and data completion rates. In addition, by collecting dynamic digital (active and passive) data, we will be able to analyze this data with respect to treatment response, remission, and relapse rates for each treatment arm. Treatment response is defined as a 50% or greater decrease in clinical symptoms (as captured by clinical assessments or self-report scales: MADRS, GAD-7, and PHQ-9); remission is defined as clinical assessment scores below the clinical threshold (e.g., MADRS  $\leq 10$ ); and relapse is characterized by the recurrence of symptoms after a patient has achieved remission (e.g., MADRS  $\geq 20$  after initial remission).

There are concerns that the use of digital platforms may affect the therapeutic relationship, yet there is a paucity of studies exploring this impact. A prior study focused on the effects of Information & Communication Technologies (ICT) in two culturally distinct countries, and the authors reported that the increased deployment of ICT facilitated patient empowerment.

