### **3.4. Concomitant Medications**

Participation in the study will not alter the standard of care, including any required changes to treatment regimens. Medications will be monitored on a regular basis and may be restricted as part of the standard of care for their respective clinical treatment. Participants will be required to

continue with their respective approved treatment for MDD throughout the study. Before the intervention, investigators will analyze all medications taken by participants on a regular basis. No medication changes, aside from the treatment received through the IPP, are allowed one month (28 days) before screening, or during the entire duration of treatment (variable based on treatment arm) and follow-up (14 days) due to the probable impact on brain activity and psychiatric symptoms. Participation in the study will not alter the standard of care, including any required changes to treatment regimens. If any changes to concomitant psychotropic medications are required as per the patient's standard of care, the participant will be withdrawn from the study.

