2. Activity information: Activity summary contains daily activity summary values and detailed activity levels. Activity levels are expressed in metabolic equivalent of task minutes (MET mins). Oura tracks activity based on the movement and presents the activity score based on duration of low, medium, and high activity levels. The movement is also used for step count and to estimate calories.
3. Readiness information: Readiness score is interpreted from sleep, activity, resting heart rate, heart rate variability, recovery index and temperature scores. A Readiness Score above 85% indicates that you're well recovered. A score below 70% usually means that an essential Readiness Contributor, such as body temperature or previous night's sleep, falls outside your normal range, or clearly differs from recommended, science-based values.

The wearable device privacy policy will be made available for all potential users to read. Data collection via the Oura Ring for selected participants will start approximately three weeks before the clinical treatment begins, continuing throughout the intervention and ending on the last day of treatment. Oura Rings will be returned to the clinical team at the end of their last treatment session.

Data collected via Oura will be de-identified using a de-identified study ID and email address which will be used to login to their account on the Oura app. This will ensure that participants are de-identified on this third-party platform (Oura).

A member of the research team will monitor data compliance on a weekly basis. If participants have Oura data that are missing for 3 or more days over the past 7 days, the clinical team will be notified so they can follow up with participants. Participants will be referred to the research team as needed to troubleshoot any technical issues.

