| Secondary Outcome | 
Clinical outcomes will be measured by:
 
 
a) Quantifying changes in active (self-report) and passive (physiological) data over time
 
b) Predicting treatment response , remission, and relapse based on active (self-report) and passive (physiological) data .
 
                                                                                                                                                                                                                                                                |

|  |                                                                                                       |
|--|-------------------------------------------------------------------------------------------------------|
|  | c) Constructing personalized digital phenotype profiles (pDPPs) based on wearable and web-based data. |
|--|-------------------------------------------------------------------------------------------------------|

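### Relapse is to be predicted and used as a comparison group, but all data collection ends at the last treatment session, so most relapses would fall outside observation

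*Protocol*

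**What the plan says.** Relapse has three roles in the protocol.

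- Section 2.2 relates active and passive data "over the duration of clinical treatment with the outcomes of treatment response", remission and relapse.
- The secondary outcome in 3.7 includes "Predicting treatment response , remission, and relapse based on active (self-report) and passive (physiological) data".
- The primary outcome box in 3.7 compares data between those who do and do not relapse.

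Section 2.1 supplies the definition: "relapse is characterized by the recurrence of symptoms after a patient has achieved remission", with MADRS of 10 or less as the example for remission and MADRS of 20 or more afterwards as the example for relapse.

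On the length of observation, 3.1 says that "each participant will only be enrolled in this study for the duration of their clinical treatment in the IPP". Section 3.6.2 has ring data collection "continuing throughout the intervention and ending on the last day of treatment", with the ring handed back at that session. Section 3.8.5.2.1 has the scales entered at study visits and treatment sessions. The last column of the schedule in 3.8.1 is the intervention.

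Two traces of a follow-up period remain. Section 3.4 bars medication changes "during the entire duration of treatment (variable based on treatment arm) and follow-up (14 days"), and the table of contents lists a follow-up section numbered 3.8.6. In the body, 3.8.5.2.2 is followed directly by 3.9.

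**The concern.** A relapse can be recorded only if the patient remits and is then rated again. A participant who remits towards the end of a course has little or no rated time left, and the protocol schedules nothing afterwards. The outcome depends on a period in which the study collects almost no data.

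At stake are the relapse part of one secondary aim and the relapse grouping in the 3.7 comparison. A model fitted to a handful of events would be uninformative. A group of participants with no recorded relapse would mix those who stayed well with those who were simply no longer observed. No analysis plan can repair this, because the outcomes would not have been collected.

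**Working it through.** The protocol gives no relapse rate, event count or follow-up length for relapse, so there is no figure of its own to reproduce. The check has two parts.

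**Part 1: rated time left after remission in the ketamine course.** Section 2.1 gives two infusions a week for three weeks, so 2 × 3 = 6 sessions. The note to 3.8.1 has the MADRS done at each session. Session days are assumed to be 0, 3, 7, 10, 14 and 17.

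| First in remission at session | Later ratings | Days left |
|---|---|---|
| 2 | 4 | 14 |
| 3 | 3 | 10 |
| 4 | 2 | 7 |
| 5 | 1 | 3 |
| 6 | 0 | 0 |

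To be recorded as a relapse, a patient must fall from 20 or more to 10 or less and return to 20 or more within those ratings. The lengths of the rTMS and ECT courses are not stated, so their windows cannot be computed. Both also end at the last session.

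**Part 2: illustrative number of observed relapses.** From the protocol: N = 200. Assumed, not from the documents: remission 30%, giving 200 × 0.30 = 60 remitters; six-month (26-week) relapse risk R of 30-60%; constant hazard; w = 1 to 4 weeks observed after remission.

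Hazard per week: h = −ln(1 − R)/26. Expected observed relapses: 60 × (1 − exp(−h·w)).

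| R | h | w = 1 | w = 2 | w = 4 | w = 26 |
|---|---|---|---|---|---|
| 30% | 0.0137 | 0.8 | 1.6 | 3.2 | 18 |
| 50% | 0.0267 | 1.6 | 3.1 | 6.1 | 30 |
| 60% | 0.0352 | 2.1 | 4.1 | 7.9 | 36 |

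The range is 0.8 to 7.9 events. Of the relapses implied over six months, the share outside observation runs from 1 − 7.9/36 = 78% to 1 − 0.82/18 = 95%.

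The four-week column is generous. It exceeds what the ketamine course allows and would apply only if another course is longer.

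A wider set of assumptions (remission 20-40%, six-month risk 30-70%, 7 to 14 days observed) gives 0.5 to 7.1 events among 200, so the conclusion does not hang on the particular rates.

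Ring users will have fewer events. Their number is not fixed: about 60 is a count of devices, and 3.8.5.2.2 has returned rings passed to further participants.

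**The case against.** The strongest reply is that this is a feasibility pilot. The association work is exploratory, relapse is one of three clinical outcomes within one secondary aim, and the primary measures do not need post-treatment follow-up. That stands, and it limits the severity. It does not justify naming an outcome that the observation window largely excludes.

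The reference in 3.1 to retrospective data analysis might suggest that later records will be used. No retrieval of post-treatment records is described, however.

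Four stronger readings are tempting, and the documents do not support them.

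- *Relapse cannot be observed at all.* Early remitters are still rated at each remaining session, and the definition in 2.1 sets no minimum duration, so return within a course can be recorded.
- *Remitters who relapse later will be counted as not having relapsed.* Section 3.7 only announces a comparison. It does not say how remitters with no later data are classified, and an analysis plan could treat them as censored.
- *Figure 1 removes precisely the people at risk.* Its caption moves patients on "In case of persistent failure to achieve clinical remission", but 3.1 and the Figure 2 caption describe one treatment per participant, and observation ends with treatment for everyone.
- *The 14 days in 3.4 already solve the problem.* No scale or ring recording is attached to them. Even if all 60 assumed remitters were observed for two weeks, the table gives only 1.6 to 4.1 events.

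**Conclusion.** The mismatch is real and visible in the protocol's own text: relapse after remission is to be predicted and compared, while enrolment, scales and ring data stop with treatment. What can be seen is symptom return during the course of an early remitter, and most relapses would fall outside observation.

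The size, about 1 to 8 observed relapses among 200 participants, is illustrative. It rests on assumed remission and relapse rates, a constant hazard and an assumed 1-4 weeks of observation after remission. The statement about ketamine sessions needs only the stated course and the rating schedule.

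This should be fixed, but it does not threaten the trial's main conclusion. The four feasibility measures, response and remission do not depend on post-treatment data.

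**What to change.** 1. Remove relapse from the association aim (trial summary and 2.2), from the prediction outcome in 3.7 and from the comparison in the primary outcome box.
2. Report symptom return during treatment among participants who remitted as a descriptive count. State that remitters are observed only to the end of treatment and are not confirmed non-relapsers.
3. Reconcile the 14-day follow-up in 3.4 and the contents entry 3.8.6 with 3.1, 3.6.2 and the schedule in 3.8.1, so that the protocol gives one account of when participation ends.

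These are wording changes and add no visits or measurements. The price is losing relapse as an inferential secondary outcome. If the sponsor wants to keep it, post-treatment depression ratings with a stated length of follow-up would have to be scheduled, with ring recording too if ring data are to be the predictor. Two weeks would yield too few events under the assumptions above. Section 3.9 places all study activities alongside clinic treatment, so this would mean additional contacts.
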